## Abstract

(1) **Background:** Swallowing disorders are common following a stroke. This study aims to evaluate the effects of a home-based daily intervention focused on inspiratory and expiratory muscle training on swallowing outcomes in patients with chronic stroke. (2) **Methods:** This manuscript presents the protocol of a single-blind randomized clinical trial. Patients with chronic stroke will be randomly assigned to either an experimental or a control group. The experimental group will undergo daily home-based respiratory muscle training in addition to standard speech and language therapy, while the control group will receive only the standard intervention. The main outcome measures will include the aspiration risk, the strength of respiratory muscles, and peak cough flow. (3) **Results:** It is hypothesized that patients receiving home-based respiratory training in addition to standard therapy will achieve significant improvements in aspiration risk, respiratory muscle strength, and cough efficacy in comparison with those included in the control group. The results will be published as a manuscript. (4) **Conclusions:** This study aims to provide evidence on the effectiveness of home-based respiratory muscle training in enhancing swallowing function and respiratory parameters in patients with chronic stroke.

## 1. Introduction

Stroke is the second leading cause of death and the third leading cause of disability worldwide [1]. Among the most frequently reported symptoms, dysphagia occurs in up to 80% of stroke survivors, with varying progression and severity [2,3]. A study conducted by Arnold et al. [4] observed that more than one in five patients with ischemic stroke suffer from swallowing dysfunction. Vasan et al. [5] also showed that approximately 10% of patients with intracerebral hemorrhage develop post-stroke dysphagia.

This dysfunction can result in social difficulties, reduced quality of life, malnutrition, dehydration, aspiration pneumonia, pulmonary complications, and recurrent coughing [2,6,7,8]. Moreover, it has been recognized as an independent risk factor linked to prolonged hospital stay, institutionalization after discharge, poorer functional recovery, and higher mortality rates. Therefore, effective management of this condition is key not only for stroke patients but also for the healthcare system [5,9].

Determining the optimal intervention for individual patients is a challenge that involves interdisciplinary work to prevent negative consequences and help the patients acquire functional swallowing [10]. Several techniques and exercises to improve swallowing ability and muscle function have been previously described. The main approach for managing swallowing dysfunction includes adapting food and fluid textures, postural techniques, compensatory techniques, and rehabilitation exercises [2,11,12,13,14,15,16]. These strategies include resistance, neuromotor, stretching, oral and lingual exercises, and myofunctional therapy [17]. Specifically, isotonic, and isometric tongue exercises, as well as lip force training have demonstrated improvement in the physiological function of oropharyngeal and submental muscles [18,19,20]. In addition, suprahyoid and infrahyoid exercises such as chin tuck against resistance (CTAR), and submandibular push have been shown to improve swallowing safety in patients with stroke [21,22]. 

Recent systematic reviews have explored the effects of respiratory training on swallowing disorders in patients with stroke, showing positive results on swallowing function and a reduction in complications such as pneumonia [23,24]. In respiratory training, patients are asked to perform repetitive breathing exercises using pressure threshold devices that provide different levels of flow-dependent resistance as external loads [25]. Respiration and swallowing share common anatomical structures and require adequate temporal coordination to ensure proper nutrition and prevent pulmonary aspiration and its sequelae [26]. Respiratory muscle weakness, a known risk factor for aspiration pneumonia, increases the risk of death by 8.5 times in individuals with chronic stroke who suffer from dysphagia compared to those without this condition [4].

Respiratory muscle training, including exercises targeting the inspiratory muscles, may increase muscle strength and improve muscle function, which is beneficial for achieving maximum lung volume at the beginning of a cough. Expiratory muscle strength training enhances the movement of the neurologically innervated submental muscle complex and increases intrathoracic pressure during coughing [16]. Although the results are promising, the effects of respiratory muscle training require further research using objective tools to quantify physiological effectiveness and better individualize training programs for patients with stroke and dysphagia. Previous studies have reported heterogeneity in the devices used, frequency, resistance, and progression of training. Moreover, several studies included in previous systematic reviews failed to provide data on these parameters and progression criteria [24,25]. 

Additionally, there is a need for studies on patients with chronic stroke, as most randomized controlled trials exploring the effects of respiratory muscle training on swallowing disorders in patients with stroke have focused on the acute and subacute stages of the disease. Although early dysphagia assessment is crucial for patient recovery [2,27], some symptoms and swallowing difficulties can persist in the long term [28]. Mao et al. [29]. identified a prevalence of 43.7% for chronic dysphagia in patients with ischemic stroke. Given the need for long-term care, rehabilitation, and community-based rehabilitation, clinical services focused on swallowing disorders are lacking [30,31]. The review conducted by Chen et al. [32] suggests that new therapy approaches, such as home-based stroke rehabilitation, could offer high-quality therapy and improve patients’ quality of life. This modality could increase the rehabilitation intensity to meet therapeutic needs without raising costs. No previous study has assessed the effects of home-based daily respiratory muscle training combined with standard therapy in patients with chronic stroke. Therefore, the objective of this study will be to evaluate the impact of a home-based daily intervention focused on inspiratory and expiratory muscle training on swallowing outcomes in patients with chronic stroke. 

## 2. Materials and Methods

### 2.1. Study Design

The research design will be a randomized, single-blind clinical trial. This study will analyze the effect of home-based daily respiratory muscle training in patients with chronic stroke presenting with swallowing dysfunction. This group will be compared with a control group. The timeline of the study is shown in Table 1, including the time point at which the enrollment and randomization procedure, assessments, and intervention will be conducted. 

### 2.2. Ethical Considerations

Written informed consent will be obtained from all the participants before enrollment in the study. In addition, the intervention was reviewed and approved by the Ethics Committee of Andalucía and conforms to the Helsinki Declaration. The study protocol has been registered at clinicaltrials.gov under the ID NCT06312319.

### 2.3. Setting 

The patients included in the study will conduct the intervention in their homes. Participants will be recruited from the Asociación Granadina de Familias por la Rehabilitación del Daño Cerebral Adquirido (AGREDACE) and the Asociación de Familiares y Enfermos de Ictus de Granada (Neuro-Afeic).

### 2.4. Participants

This study will include patients with a clinical diagnosis of stroke and dysphagia. Inclusion criteria will be as follows: age of 18 years old or over, and chronic stroke, defined as an open-ended period of ≥6 months’ duration since stroke diagnosis [33]. The exclusion criteria will include a clinical diagnosis of a concomitant neurological condition, co-occurring aphasia, severe cognitive impairment (Montreal Cognitive Assessment [MoCA] < 26 points) [34], tracheostomy, cancer, lack the neuromotor ability to perform respiratory function tests, central apnea, obesity-hypoventilation syndrome, or significant cardiorespiratory conditions such as hemodynamic instability, pulmonary embolism, recent pneumothorax, acute hemoptysis, active respiratory infections, recent myocardial infarction, unstable angina, pulmonary hypertension, uncontrolled asthma, or severe chronic obstructive pulmonary disease. Additionally, patients who have recently undergone otorhinolaryngological, abdominal, or thoracic surgery will be excluded.

### 2.5. Randomization

Participants in this study will be randomly assigned (1:1 ratio) to either an experimental or a control group. The eligibility of participants will be assessed by an independent researcher not involved in the randomization process. The randomization will be performed by a researcher not involved in the study procedure. The randomization sequence will be generated by a computer program (https://www.randomizer.org). The assessment will be carried out by a therapist blinded to the treatment assignments.

### 2.6. Intervention Protocol

Patients allocated to the experimental group will participate in a 6-week home-based respiratory muscle training program in addition to the standard speech and language intervention. Patients in the control group will receive only the standard intervention. The protocol of both interventions is illustrated in Figure 1. 

#### 2.6.1. Respiratory Muscle Training

Respiratory muscle training will be performed using a calibrated Expiratory Muscle Strength Trainer (EMST-150) and an inspiratory adapter (IA-150) (EMST 150; Aspire Products, Gainesville, FL, USA). 

In a previous in-person session, patients will be trained to use the device. They will be instructed to sit in a proper position in a chair, wear nose clips, take a deep breath, hold their cheeks lightly, blow as hard as they can into the device, and ensure that air flows freely through the device. Written instructions with pictures and text will also be provided to each patient.

The home-based respiratory training sessions will consist of two sets of 15 breaths (15 repetitions of inspiratory muscle training and 15 repetitions of expiratory muscle training) with 2 min of recovery between the sets. Training will be conducted twice daily, 5 days per week for 6 weeks, at the same time each day. Training loads will be set at a pressure equivalent to 30% of maximal inspiratory and expiratory pressures and will be increased weekly at intervals of 10 cmH_2_O [35,36]. This resistance will be readjusted if needed according to the patient’s tolerance. The number of repetitions will also increase starting from the third week to a maximum of 5 sets of each inspiratory and expiratory exercise per day, as tolerated. Patients will complete a diary indicating the number of repetitions per day and the time of day. Additionally, patients will use a visual analog scale from 0 to 10 to rate their symptoms of fatigue, dizziness, or pain during the training, where 0 represents no symptoms and 10 represents maximal severity. Once per week, the patient will have a video call from the therapist to review the diary and any symptoms that appeared during training, adjust the progression, and resolve any doubts. Adherence will be assessed using this diary. 

#### 2.6.2. Standard Speech and Language Therapy

All patients will receive standard speech and language interventions for one hour per day, 3 days per week for 6 weeks. The intervention will include (1) education focused on dysphagia and airway protection, including how to modify food and fluid textures; (2) postural and compensatory techniques; (3) tactile and thermal stimulation with different temperatures, flavors, and textures; (4) strength and resistance training including isotonic and isometric exercises such as CTAR or submandibular push; and (5) functional exercises based on videofluoroscopic findings [37]. The frequency and intensity of the exercises will be individualized, taking into account the safety level and the types of food that patients can eat safely, with modifications to texture if necessary. Attendance will be registered weekly.

### 2.7. Outcomes

At baseline, clinical and demographic data will be recorded, including age, sex, height, weight, academic studies, the side, site, and the dimension of the cerebral lesion based on the Fugl-Meyer Upper and Lower Extremity scales [38]. Additionally, disease duration and the type of stroke, whether ischemic or hemorrhagic, will be noted. In cases of ischemic stroke, the type of recanalization therapy will be specified. The initial evaluation will be performed once informed consent is obtained. The assessment will be conducted by a blinded therapist with previous experience in treating patients with stroke. 

#### 2.7.1. Main Outcomes

The main outcomes will include the aspiration risk, the strength of respiratory muscles, and peak cough flow. 

The penetration or aspiration risk will be assessed using the Penetration–Aspiration Scale (PAS) [39]. The PAS is a valid and reliable 8-point scale used during videofluoroscopy assessment. It evaluates the depth of airway invasion, the material remaining after swallowing, and the patient’s response to aspiration. The scores range from 1 (material does not enter the airway) to 8 (material enters the airway, passes below the level of the vocal folds, and no effort is made to eject it). The assessment will be conducted by two experienced researchers, who are blinded to the swallowing performance before and/or after the targeted swallow task. This scale has been reported to be a valid tool for differentiating between normal and abnormal airway protection [39]. 

Respiratory muscle strength will be evaluated using maximal inspiratory pressure (MIP) and maximal expiratory pressure (MEP) measurements [40]. The patients will be evaluated in a sitting position while wearing a nose clip. To evaluate the MIP, the patients will be instructed to exhale air near the residual volume and then inhale through the mouthpiece. To measure MEP, the patients will be asked to inhale air near total lung capacity and then exhale the air through the mouthpiece. Three maneuvers will be performed, ensuring no more than a 20% difference among them [41]. The cut-off values to determine muscle weakness are 62 and 83 cmH_2_O for MIP in females and males, respectively, and 81 and 109 cmH_2_O for MEP in females and males, respectively [42].

Voluntary peak cough flow (L/min) will be evaluated using a peak flow meter (Micro Medical, Cambridge, UK) [43]. This parameter assesses the maximum expiratory flow during a cough to evaluate the efficacy of secretion clearance. The patient will be seated in a chair, will inhale as much air as possible, and then cough as forcefully as possible through the mouthpiece. The maneuver will be performed three times, and the mean of the values will be included in the analysis. Standardized values in healthy adults range between 360 and 400 L/min [44]. An effective cough is associated with having a peak flow rate of over 160 L/min, while a rate below 270 L/min is associated with increased secretion retention and a higher risk of infection [45].

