### 2.8. Sample Size Calculation

The sample size was calculated using G*Power software, version 3.1.9.2. Based on a previous study, our control group’s expected post-treatment PAS score is 4.62 ± 0.77 [48]. According to a power calculation of 80% and assuming a clinically relevant difference of one point on the PAS score between the study groups, with a standard deviation of 1.2 [49], we determined a total sample size of 55 participants. The calculation is based on an alpha level of 95%, accounting for a 15% dropout rate.

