### 2.9. Statistical Analysis

Data will be analyzed using the Statistical Package for the Social Sciences (SPSS) for Windows (version 26, IBM, Armonk, NY, USA). Categorical data will be reported as frequencies and percentages, while continuous variables will be summarized using means and standard deviations. The Shapiro–Wilk test will be used to assess data normality. Differences between groups will be examined with the Chi-square test for categorical variables. For continuous variables, Student’s t-test will be applied for normally distributed data, and the Mann–Whitney U test will be used for non-parametric data. Effect sizes will be calculated using Cohen’s d, with the following values: a small effect is indicated by 0.3, a moderate effect is indicated by 0.5, and a large effect is indicated by 0.8.

Statistical significance will be determined at *p* < 0.05. Participants with adherence rates of 80% or less, based on home diaries and attendance to standard speech and language sessions, will be excluded from the statistical analysis.

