## 4. Discussion

This study aims to evaluate the impact of a home-based daily intervention focused on inspiratory and expiratory muscle training on swallowing outcomes in patients with chronic stroke. It is hypothesized that patients receiving home-based respiratory training in addition to standard therapy will achieve significant improvements in aspiration risk, respiratory muscle strength, and cough efficacy.

Post-stroke dysphagia can cause health-related problems throughout a patient’s life and is linked to increased healthcare costs [50]. In this context, this study aims to increase the intensity of therapy by using a home-based approach in addition to standard intervention. Implementing home-based interventions allows patients to reduce the frequency of hospital visits. Additionally, with continuous monitoring and personalized care plans, patients with dysphagia often experience better health outcomes and a reduced need for emergency interventions related to respiratory complications [32,50,51].

Previous studies [52,53] have assessed the effects of home-based exercises for patients with dysphagia. Yang et al. [52] conducted a systematic review of home-based telerehabilitation for dysphagia in patients with head and neck cancer. They observed improvements in swallowing safety, adherence to rehabilitation, and quality of life related to swallowing dysfunction. Moreover, the home-based approach demonstrated good efficiency and low costs compared with face-to-face interventions [52]. Additionally, a study involving respiratory muscle training was conducted in patients with Parkinson’s disease presenting with dysphagia using a home-based approach [46]. The authors reported that four-week expiratory muscle strength training significantly reduced dysphagia severity, with a sustained effect after 3 months compared to sham training [53]. In this protocol, we present a home-based approach based on respiratory training for patients with chronic stroke and dysphagia.

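### Four measures serve as equal main outcomes at p < 0.05 with no success rule, while the trial is sized on PAS alone; if any one suffices, the false-positive risk exceeds 5%

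*Protocol article*

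**What the plan says.** Section 2.7.1 sets the main outcomes: "The main outcomes will include the aspiration risk, the strength of respiratory muscles, and peak cough flow". It then splits one of them in two: "Respiratory muscle strength will be evaluated using maximal inspiratory pressure (MIP) and maximal expiratory pressure (MEP) measurements". With PAS and peak cough flow, that makes four variables, none ranked above another. Section 2.7.2 lists the secondary outcomes separately (FOIS and SWAL-QOL).

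Section 2.9 gives one threshold for all comparisons: "Statistical significance will be determined at *p* < 0.05". It states no order, adjustment or rule for combining the main outcomes.

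Section 2.8 bases the sample size on one of the four, "assuming a clinically relevant difference of one point on the PAS score between the study groups", with SD 1.2, 80% power and 15% dropout, giving 55 participants. It gives no effect size or SD for MIP, MEP or peak cough flow.

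The hypothesis in the Abstract and section 4 is that the experimental group will "achieve significant improvements in aspiration risk, respiratory muscle strength, and cough efficacy". The objective in sections 1, 4 and 5 is the effect on swallowing outcomes. Section 3 mentions primary and secondary measures without singling out one primary.

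**The concern.** The plan does not define what result makes the trial positive, and the two natural readings fail differently. If any main outcome is enough, four unadjusted tests at 0.05 give more than a 5% chance of a false claim. If all are needed, the 80% power computed for PAS does not describe the chance of success.

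A second issue concerns interpretation rather than error rates. PAS is the only main outcome that measures swallowing. Section 2.6.1 has the experimental arm training twice a day against inspiratory and expiratory loads set as a percentage of the maximal pressures that MIP and MEP measure. Those measurements depend on effort. Under section 2.6 controls receive standard therapy only, with no sham device, so participants will know their arm. MIP or MEP could improve with no change in PAS, and the plan as written would let that stand as a positive main outcome.

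**Working it through.** **1. Reproduce the stated sample size (section 2.8)**

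Inputs: difference 1 point, SD 1.2, power 80%, 1:1 allocation (section 2.5), dropout 15%. The article writes "The calculation is based on an alpha level of 95%, accounting for a 15% dropout rate"; I read this as alpha 0.05, two-sided.

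- n per arm = 2 × (1.96 + 0.8416)² × 1.2² / 1² = 22.6, rounded up to 23, so 46 in total.
- 46 / 0.85 = 54.1, rounded up to **55**, as stated.
- With the noncentral t: 24 per arm, 48 in total. Then 48 / 0.85 = 56.5, or 57; 48 × 1.15 = 55.2.
- A one-sided test gives 43 to 45 and does not reproduce 55.

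So 55 is what PAS alone needs at the full two-sided 5%. No alpha was set aside for other main outcomes.

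**2. Any one is enough**

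For k independent tests at 0.05 with all k nulls true, the family-wise error is 1 − 0.95^k.

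| Scenario | Family-wise error |
|---|---|
| Four tests, independent | 1 − 0.95⁴ = 18.5% |
| Four tests, common correlation 0.3 (simulated) | 17.4% |
| Four tests, 0.5 (simulated) | 15.6% |
| Four tests, 0.7 (simulated) | 13.1% |
| Four tests, 0.9 (simulated) | 9.4% |
| Strength counted as one test, three independent | 1 − 0.95³ = 14.3% |
| MIP and MEP truly improve; PAS and cough flow null, independent | 1 − 0.95² = 9.75% |

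The correlations are assumptions; the article gives none. The simulations use jointly normal statistics with equal correlations. For two-sided tests on jointly normal statistics 18.5% is the maximum; under arbitrary dependence the bound is 4 × 0.05 = 20%.

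**3. All are needed**

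The family-wise error does not exceed 5%. Joint power depends on the power for MIP, MEP and cough flow, and no inputs are given for these, so it cannot be computed. As an illustration only, assume 80% power on each:

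- independent: 0.8⁴ = 41%;
- common correlation 0.3: 50% (simulated);
- common correlation 0.5: 56% (simulated).

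If power on the trained measures were above 80%, these figures would rise.

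**4. Two ways to repair it**

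- PAS as sole primary at two-sided 5%: the sample size stays at 55.
- Four co-primaries with Bonferroni: 0.05 / 4 = 0.0125 each. Sized on PAS this needs 34 per arm by the t-test, 68 in total, and 68 / 0.85 = 80 with dropout. With 24 evaluable per arm, PAS power falls from 80.7% to 61.4%.

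**The case against.** The strongest reply is that the article never says one significant result is enough. The hypothesis joins the three domains with *and*, and under an all-must-succeed rule error does not inflate. PAS is also listed first, is the only outcome behind the sample size, and is the only one that matches the objective, so it may already be the intended lead. Testing order and multiplicity are often left to a statistical analysis plan, which is not shown here. The assessor is blinded, and the pressure manoeuvres must agree within 20%.

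Much of this limits the point without removing it. The hypothesis is an expectation, not a decision rule. PAS is the implied lead, but the article gives four variables equal status and one threshold; that is a stated choice, not silence. Assessor blinding and repeatability limits do not remove the effect of effort by participants who know their arm.

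Three stronger readings are tempting but unsupported:

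- A reader might infer that the trial's false-positive risk simply is 18.5%. That needs three conditions: any one result suffices, all four nulls are true, and the tests are independent. Independence is unlikely for effort-based respiratory measures.
- A reader might infer that the stated 80% power is wrong. Section 2.8 claims it for PAS only, and there it reproduces.
- A reader might count a MIP or MEP gain from training among the false positives. A true gain is not a false positive; the difficulty is what it says about swallowing.

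**Conclusion.** The point holds in conditional form. The article fixes three equal main outcomes measured by four variables, one unadjusted threshold, a sample size for PAS only, and no success rule.

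If any one result suffices, the family-wise error is above the nominal 5% in every scenario examined. It runs from 18.5% (four true nulls, independent tests) down to 9.4% (four true nulls, assumed correlation 0.9), and is 9.75% when only PAS and cough flow are null and independent. If all must succeed, error is controlled but the power of the joint claim is unknown; 41% to 56% is illustrative only. Under either reading, a positive MIP or MEP result would not in itself answer the swallowing question. The needed change is small, but it should be made before any unblinded outcome data are seen.

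**What to change.** In section 2.7.1, name post-intervention PAS as the single primary outcome, tested at two-sided 5%, and state that the trial's conclusion rests on it. Make MIP, MEP and peak cough flow secondary outcomes, tested only if PAS is significant, with Holm adjustment across the three. State this in section 2.9, and align the Abstract and the hypothesis in section 4. The registry entry was not available for this review; check it for consistency.

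Keeping several co-primary outcomes is defensible if a success rule is stated. With Bonferroni over four it would need about 80 participants instead of 55; with an all-must-succeed rule it would need design inputs for the other three measures.

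The recommended change costs wording only: no extra participants or data. Its downside is that a gain in muscle strength or cough flow alone can no longer be claimed as trial success.
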